## Abstract

Adequate sleep health is critical for surgical recovery. Disrupted sleep can impede wound healing and cognitive performance and contribute to poor surgical outcomes. Preoperative intervention aimed at improving surgical outcomes is often referred to as prehabilitation and commonly uses exercise, nutrition or psychological intervention. Sleep prehabilitation interventions have not yet been studied. This randomised assessor‐blinded trial will measure the effect of a personalised sleep prehabilitation (PSP) intervention in addition to standard of care prehabilitation (PREHAB) on participant sleep health compared to PREHAB alone (Clinicaltrials.gov ID: NCT06762639). One hundred fifty‐four English‐speaking patients from the University Health Network's Prehabilitation Program with sleep disturbance and a surgery within 4–12 weeks will be recruited. Patients will be excluded if they are participating in PREHAB remotely, have an existing sleep disorder, are a shift worker, have travel plans outside of their usual time zone or have a cognitive disability that precludes participation. Study assessments occur at baseline, 1 week before surgery and 6 weeks after surgery. PREHAB consists of individualised exercise and nutrition support as well as psychological intervention. The PSP consists of a baseline sleep assessment, brief behavioural treatment for insomnia (BBTI), sleep hygiene and behaviour‐change support. The primary outcome is the Pittsburgh Sleep Quality Index (PSQI). The primary analysis will be an ANCOVA to detect differences in PSQI between groups 1 week before surgery whilst controlling for baseline scores. The proposed study will be the first to explore the effect of a personalised preoperative sleep intervention.

## Introduction

1

Sleep health is a well‐established determinant of overall health. Short sleepers (< 7 h per night) experience higher rates of diabetes, hypertension, cardiovascular disease, obesity and mortality (Itani et al. 2017). In the perioperative period, adequate sleep is requisite for optimal immune function, wound healing, energy metabolism and cognitive performance (Mukherjee et al. 2015). Impairment of these processes due to inadequate sleep can impede recovery and contribute to poor surgical outcomes (Gillis et al. 2022). For example, a recent meta‐analysis of 18 studies demonstrated that pre‐ or postoperative sleep disturbance substantially increased the risk for postoperative delirium (OR: 3.7; 95% CI: 2.3–6.0) (He et al. 2022). Disrupted preoperative sleep is also an independent risk factor for morbidity and a longer hospital length of stay (Kehlet 1997). An observational study of total hip arthroplasty patients showed that preoperative sleep quality predicted opioid consumption during the first 24 h after surgery (β = 0.009 [95% CI 0.002–0.015] mg/kg, *p* = 0.007, R^2^ = 0.15) and subjective pain assessment 6 months after surgery (β = 0.091 [95% CI 0.001–0.181], *p* = 0.048, R^2^ = 0.35) (Bjurström et al. 2021). Patients with obstructive sleep apnea, a condition resulting in impaired sleep quality, experience a 47% increased risk for major cardiac and pulmonary complications (Memtsoudis et al. 2014). Despite the relationship between preoperative sleep health and postoperative outcomes, sleep health disturbances are not routinely measured or addressed (Wolfe et al. 2016). This is alarming given that 60% of patients have disturbed preoperative sleep (Butris et al. 2023).

Increased pain, morbidity and hospital length of stay due to disturbed sleep health may result in increased patient and healthcare resource burden. Accordingly, optimising preoperative sleep health is a promising avenue for improving surgical care. Different approaches have been used to improve sleep health before or after surgery, though the majority of interventions have been delivered in the acute postoperative period (Machado et al. 2017). One systematic review of 10 randomised controlled trials (RCTs) used non‐pharmacological interventions such as relaxation techniques (e.g., massage), equipment or devices (e.g., music) and education to improve sleep in the acute postoperative period amongst cardiac patients (Machado et al. 2017). Whereas these data highlight the ability of interventions to mitigate or recover losses to sleep health, the preoperative period may represent a time to improve sleep health such that there is resilience to the deficit to sleep health incurred with surgery. Further, several documented causes of poor sleep postoperatively may be most appropriately addressed preoperatively, including pain, anxiety and inactivity (Memtsoudis et al. 2018). As such, intervening on sleep health exclusively in the postoperative period may miss a salient opportunity to improve surgical care.

Preoperative intervention aimed at improving surgical outcomes is often referred to as prehabilitation. Prehabilitation may include one or a combination of preoperative exercise, nutrition and psychological intervention to improve physical, psychosocial and clinical outcomes before and after surgery. While these modalities have been associated with improved sleep health outside of the surgical context, a recent RCT of prehabilitation versus usual care revealed no differences in sleep health (Atoui et al. 2023). As such, targeted sleep interventions initiated preoperatively are warranted.

Cognitive behavioural therapy for insomnia (CBT‐I) is the gold‐standard non‐pharmacological intervention for sleep disturbance (Brasure et al. 2016). Meta‐analyses have established and confirmed CBT‐I as an effective treatment for insomnia (van der Zweerde et al. 2019; Hofmann et al. 2012). Brief behavioural treatment for insomnia (BBTI) is a derivative of CBT‐I that may be particularly useful within prehabilitation due to its expeditious delivery without the requirement for specialised interventionists. A recent systematic review of 47 preoperative interventions that measure a sleep outcome revealed no interventions employed CBT‐I or BBTI (Sibley et al. 2024). As such, despite the high prevalence of preoperative sleep disturbance and the availability of established, effective non‐pharmacological treatments, no study has assessed the independent effect of an individualised sleep intervention before surgery.

## Objectives

2

The primary objective of this study is to evaluate the effectiveness of a personalised sleep prehabilitation (PSP) intervention in addition to standard‐of‐care multimodal prehabilitation (PREHAB) on participant sleep health versus standard‐of‐care multimodal prehabilitation alone (i.e., PSP+PREHAB vs. PREHAB). Secondary objectives include examining the impact of the intervention on anthropometric, physical fitness, patient‐reported, clinical and other sleep health outcomes. A full list of study research questions is available in Appendix S1.

## Methods

3

### Study Design and Setting

3.1

This is a randomised trial conducted at the surgical Prehabilitation Program at the University Health Network (UHN), a large tertiary academic hospital network in Toronto, ON. Participants will be randomised 1:1 to intervention (PSP+PREHAB): active comparator (PREHAB). Flow of participants is depicted in Figure 1. The initial study protocol has been approved by the University Health Network Research Ethics Board. The trial is registered with ClinicalTrials.gov (ID NCT06762639). This protocol was reported in adherence with the Standard Protocol Items: Recommendations for Interventional Trials (SPIRIT) checklist (SPIRIT 2013 Checklist: Recommended Items to Address in a Clinical Trial Protocol and Related Documents n.d.). The checklist is available in the Supporting Information (Appendix S2).

**FIGURE 1 jsr70173-fig-0001:**
[figure not shown]
Study flow diagram. PREHAB, multimodal prehabilitation consisting of exercise and nutrition intervention; PSP, personalised sleep prehabilitation. Preoperative assessment occurs within 1 week of surgery. Postoperative assessment occurs 6 weeks after surgery (±1 week).

### Participants

3.2

Participants will be eligible if they are referred to the UHN Prehabilitation Program; this includes adults (18 years of age or older) referred by a healthcare provider due to elevated surgical risk (most commonly due to frailty). Other inclusion criteria are as follows: (i) surgery date is 4–12 weeks from the time of consent, and (ii) having existing sleep disturbance. An operational definition of sleep disturbance is available in Appendix S3. Exclusion criteria are as follows: (i) an existing diagnosed sleep disorder that is poorly managed or requires referral to a sleep clinician, (ii) currently a shift worker (work schedule outside of 7 am–6 pm), (iii) plans to travel 3 or more hours outside of their usual time zone, (iv) does not have English proficiency, and (v) has a cognitive disability that significantly limits ability to respond to screening questions or adhere to the intervention.

### Sample Size

3.3

A total of 154 participants will be recruited for this study. The sample size was computed by a biostatistician at UHN for an ANCOVA design in which the Pittsburgh Sleep Quality Index (PSQI) score will be compared between the two arms at the preoperative timepoint, controlling for baseline scores. Assuming a PSQI score mean of 11.9 (SD 2.6) points for the usual care arm (Atoui et al. 2023) with no correlation between baseline and preoperative scores, a sample size of 64 participants per arm (128 total) will be required to detect a difference in mean PSQI score of 1.3 points, which is the minimum clinically important difference (Longo et al. 2021). This difference between the two arms corresponds to a Cohen's d effect size of 0.5 with 80% power and an alpha of 0.05. The final sample accounts for 20% attrition.

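### The recruitment total of 154 covers 16.9% attrition, not the stated 20%; at 20% loss, power on the plan's own inputs is 78.5% rather than 80%

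*Protocol article*

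**What the plan says.** Section 3.3 (Sample Size) of the protocol article gives the whole calculation in one paragraph.

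- Recruitment target: "A total of 154 participants will be recruited for this study".
- Evaluable number: "a sample size of 64 participants per arm (128 total) will be required to detect a difference in mean PSQI score of 1.3 points".
- Outcome assumptions: "Assuming a PSQI score mean of 11.9 (SD 2.6) points for the usual care arm", and "with no correlation between baseline and preoperative scores".
- Error rates: "with 80% power and an alpha of 0.05".
- Step from 128 to 154: "The final sample accounts for 20% attrition".

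The formula for that last step is not shown. The comparison being sized is the ANCOVA on PSQI at the preoperative timepoint, with 1:1 allocation.

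**The concern.** An attrition allowance is a promise about the participants who are enrolled: if the stated share of them is lost, the number needed for analysis is still there. For a required 128 and a 20% loss, that means dividing by 0.80. The published total is smaller than the result of that division and equals 128 plus 20% of 128. If so, 154 recruited, 20% attrition and 80% power at 1.3 points cannot all hold together under the plan's own assumptions.

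This is the sample size for the primary outcome, aimed at the difference the protocol treats as minimally important. Anyone monitoring retention would read 20% as a safe limit, when the evaluable number falls short at a lower rate of loss. The Discussion also says that, without a formal published feasibility trial, adherence is hard to predict, so the allowance should mean what it says.

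**Working it through.** **Inputs, all from section 3.3 unless noted.** Difference 1.3; SD 2.6; baseline–preoperative correlation 0; power 80%; alpha 0.05; 64 per arm (128); total 154; attrition 20%. Allocation 1:1 is from section 3.5. Sidedness is not stated. I take it as two-sided because that reproduces 64 per arm, whereas a one-sided test needs only about 50.

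**Step 1: reproduce the evaluable number.** d = 1.3/2.6 = 0.5. With zero correlation, ANCOVA gains nothing over a two-sample t-test, so power comes from the noncentral t distribution with noncentrality d/√(1/n₁ + 1/n₂).

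- 63 per arm: noncentrality 0.5/√(2/63) = 2.81, power 79.5%.
- 64 per arm: noncentrality 0.5/√(2/64) = 2.83, power 80.1%.

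So 64 per arm is the smallest number that reaches 80%. The plan's base figure is correct, and it has almost no slack.

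**Step 2: reproduce the total.**

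- Allowing for a loss from those enrolled: 128/(1 − 0.20) = 160.
- Adding 20% to the evaluable number: 128 × 1.20 = 153.6, rounded up to 154.

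Only the second gives the published total.

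**Step 3: what 154 delivers.**

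- At 20% loss: 154 × 0.80 = 123.2, so 123 evaluable, about 62 and 61 per arm. That is 128 − 123 = 5 short.
- Largest loss that still leaves 128: 1 − 128/154 = 26/154 = 16.9%.

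**Step 4: power at 62 and 61.** Noncentrality = 0.5/√(1/62 + 1/61) = 2.77, which gives power of 78.5%. Removing one degree of freedom for the baseline covariate does not change this to the first decimal.

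| Evaluable | Power at 1.3 points | Difference detectable with 80% power |
|---|---|---|
| 64 + 64 | 80.1% | 1.30 |
| 62 + 61 | 78.5% | 1.32 |

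**Step 5: sensitivity to the zero-correlation assumption.** With correlation r, adjusting for baseline reduces the residual SD by √(1 − r²), so the effective d is 0.5/√(1 − r²). The document gives no value of r, so those below are assumptions. Power at 62 and 61:

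| r | Power |
|---|---|
| 0 | 78.5% |
| 0.1 | 78.9% |
| 0.2 | 80.2% |
| 0.3 | 82.2% |
| 0.5 | 88.8% |

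The shortfall closes at r of about 0.2.

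**The case against.** The strongest reply is that the consequence is close to nil. Power drops by about 1.6 points (80.1% to 78.5%) and the detectable difference moves by about 0.02 to 0.03 PSQI points. Even that exists only under a conservative assumption, since any positive correlation between baseline and preoperative PSQI raises the power of the ANCOVA. This stands as a statement about size, and nobody should call the trial seriously underpowered on this ground. It does not rescue the sentence, because the plan fixed the correlation at zero and its claim has to hold on its own inputs. If the sponsor relies on a positive correlation, the protocol should say so.

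A second reply is that the section does not say when the 20% accrues. Table 2 tracks attrition through to six weeks after surgery, whereas the primary comparison is before surgery. If 20% is the whole-study figure and no more than 26 of the 154 are lost by the preoperative visit, 128 remain and the stated power holds. That is possible, but the section sizes the trial at the preoperative timepoint and applies the allowance to that number without distinguishing the two, so the natural reading is attrition at the primary endpoint.

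Third, multiplication by 1.20 is an inference, because no formula is printed. That is correct. It is the only standard route to 154, but the contradiction does not depend on it: however 154 was reached, it covers 16.9%. Nor is this a detail that an article would leave to a fuller document, since all the figures that disagree are printed in the same paragraph.

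**Conclusion.** The concern holds. On the protocol's own figures, 154 recruited participants protect the required 128 against attrition of up to 16.9%, not 20%. At 20% loss before the preoperative assessment, 123 remain and power for 1.3 points is 78.5%, against 80.1% at the required number. Full cover for 20% would need 160, six more than planned.

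This rests on a two-sided test at 0.05, SD 2.6, zero baseline correlation, loss spread roughly evenly over the arms, and the 20% being reached by the primary timepoint. It is a definite error in a key design statement with a modest effect. It should be corrected, but it does not threaten the design.

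**What to change.** Keep 154 and replace the last sentence of section 3.3 with one that is true. Either of these will do:

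- the final sample allows for up to 16.9% attrition by the preoperative assessment while keeping 80% power; or
- with 20% attrition by that assessment (123 evaluable), power to detect 1.3 points is 78.5% at zero baseline correlation.

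If the sponsor wishes to add that baseline adjustment is likely to recover the shortfall, the correlation relied on and its source should be given. About 0.2 is enough. The cost is one sentence and a slightly less favourable attrition or power figure, with no extra participants.

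The alternative is to raise the target to 160 (80 per arm). The present sentence then becomes correct, since 160 × 0.80 = 128, at the cost of six more participants.

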### Sampling and Recruitment

3.4

Participants will be recruited from the Prehabilitation Program at Toronto General Hospital based on the usual referral criteria. Patients who are eligible for the UHN Prehabilitation Program are those with a scheduled surgery at UHN and referred by a member of their circle of care. Upon referral, a member of the patient's circle of care will briefly introduce the study and inquire if the patient is interested in hearing more. If agreeable, a member of the research team will contact the patient to discuss the study protocol, potential risks and benefits to participation and answer patient questions. If the patient is interested, the research team member will initiate the informed consent process.

### Randomisation and Blinding

3.5

Participants will be randomised 1:1 (PSP+PREHAB: PREHAB) using a computer‐generated randomisation sequence. This randomisation process will be blinded such that the research team member who generates the randomisation sequence is not in contact with interventionists, outcome assessors or the participant's circle of care. Due to the nature of the study, participant and interventionist (PSP) blinding is not possible. However, outcome assessors and clinicians delivering PREHAB will be blinded to group allocation.

### Standard of Care Prehabilitation (PREHAB)

3.6

All participants (both study arms) will receive standard of care multimodal prehabilitation (PREHAB) from consent until surgery. All participants will undergo a baseline assessment consisting of a verbal interview and physical function assessment to ascertain medical history, functional capacity and relevant information required to individualise PREHAB (Table 1). The PREHAB model of care has been published previously (Randall et al. 2024). PREHAB consists of exercise prehabilitation and nutritional prehabilitation for all participants. Psychological and smoking cessation prehabilitation is delivered to patients screening positive using standardised screening tools. Prehabilitation modalities are summarised below and detailed in Appendix S4.

**TABLE 1 jsr70173-tbl-0001:** PREHAB baseline assessment.

Assessment component	Description
Health history and intervention needs screen	Comorbidity collection (CCI), Frailty (Edmonton Frail Scale; EFS), Nutrition risk via the CNST Sleep via the Global Sleep Assessment Questionnaire (GSAQ).
Body composition	Body mass in kilogrammes using a standing digital scale Height in centimetres using a wall‐mounted stadiometer Body mass index (calculated) body fat %, lean mass and fat mass measured with the mBCA 514 (Seca, Hamburg, Germany)
Functional capacity	Grip strength via hand grip dynamometer Timed up and go Short physical performance battery Six‐minute walk test

Exercise Prehabilitation: Exercise‐based prehabilitation will be instructed and delivered by a Registered Kinesiologist. The exercise prescription will be tailored to the results and observations obtained during the baseline assessment. The aerobic training will be light to moderate intensity continuous training (MICT) at 40%–70% of heart rate reserve (HRR, estimated based on age‐predicted HR_max_ and resting heart rate) or approximately four to six on the 10‐point rating of perceived exertion (RPE) scale. The default modality of aerobic exercise is walking. Muscular fitness will be targeted through a minimum of 3–5 resistance training exercises per session targeting major muscle groups (4–6/10 RPE). A standard linear progression will be targeted using the goal of achieving 3 sets of 8–15 repetitions per exercise with a minimum of 24 h of recovery between resistance training sessions. Progression in resistance intensity will occur when 15 repetitions of a given exercise can be completed with only mild exertion (< 4/10 RPE). All exercises will be demonstrated in the Prehabilitation Program facility where participants will have an opportunity to practise and receive feedback or alternate exercises. Exercise prescriptions will target a total volume of 150 min of moderate to vigorous aerobic exercise and 2 sessions of resistance training per week, though this will be individualised based on the results of the baseline assessment. Exercise prescriptions are intended to be completed unsupervised and in the home, but will be modified to support supervised delivery or completion in other settings (e.g., condominium gym).

Nutritional prehabilitation: A registered dietitian (RD) will provide an individualised nutrition assessment and counselling session within the first week of prehabilitation and again in the week prior to surgery (if indicated). Each consultation will be 30–60 min in length and can be conducted in person or via telephone. The patient's nutritional history (via 3‐day diet record), assessment of usual intake and weight history will be reviewed to help identify any nutritional issues or concerns. The session will focus on the goals of nutrition during prehabilitation and in the post‐surgical period by providing strategies to help the patient optimise or enhance the nutritional quality of the diet, maintain a healthy weight and minimise weight gain or weight loss, and address any nutrition‐related questions or concerns. Participants will be informed of the healthy eating recommendations described by the Canada Food Guide. Participants will also be educated on maintaining and/or intaking adequate protein levels (1.2 g/kg/day) to mitigate age‐related muscle depletion and support optimal muscle health. The participant will be encouraged to contact the RD as needed during treatment for ongoing support of any nutrition‐related questions or concerns.

Psychological prehabilitation: If indicated, within 1 week of initiating prehabilitation, a Clinical Psychologist or trainee in supervised practice will deliver a 30–60‐min psychoeducation session that focuses on stress management via relaxation, mindfulness, goal setting and strategies to overcome barriers to practice. In the week prior to surgery, participants will be offered a second consultation with the psychology team member to review their stress management experiences and provide further support for the acute perioperative period. These sessions will also incorporate behaviour change support counselling, based on theoretical models such as Motivational Interviewing, the Trans‐Theoretical Model, Social Cognitive Theory and the Theory of Planned Behaviour (Prochaska and Di Clemente 1982; Bandura 1977; Ajzen 1991). Psychology sessions may be delivered in person or remotely via telephone or Microsoft Teams (Microsoft Corporation, Redmond, WA, USA).

Smoking Cessation: Participants who smoke will be provided with education regarding the impact of preoperative smoking on surgical recovery. Participants will be referred to UHN's smoking cessation programme for one‐on‐one counselling using non‐pharmacological and pharmacological smoking cessation techniques delivered by a pharmacist.

### Personalised Sleep Prehabilitation (PSP)

3.7

In addition to the standard of care multimodal prehabilitation described above, intervention arm participants will also receive a PSP intervention. The ultimate goal of the PSP is to improve patient sleep health encompassing regularity, quantity and quality (Gunn et al. 2019). The main element of the PSP is BBTI. The 4 intervention sessions will follow the content of BBTI as outlined by Gunn et al. (2019) and Troxel et al. (2012). A participant‐facing researcher‐developed BBTI package will be provided to participants that outlines the crucial components of the intervention (Buysse et al. 2011; Germain et al. 2006). The intervention will be modified such that it can be delivered entirely remotely to ensure feasibility at our site and promote equitable access to health resources. In addition to BBTI, the intervention will consist of sleep hygiene and behaviour change modification. The intervention will be delivered once weekly for 4 weeks lasting 20–60 min per session and delivered one on one. The intervention will be delivered by a regulated health professional (RKin or CPsych) with training and experience delivering primary care sleep intervention. The PSP is tailored to the needs, preferences and context of the participant as identified during the baseline sleep assessment and using a shared decision‐making approach between the research member and participant. These intervention components are described further below.

Baseline assessment: The baseline assessment will consist of a review of participant responses to the Global Sleep Assessment Questionnaire (GSAQ). Results of the screening will be used to initiate a discussion regarding participant sleep habits and behaviour.

BBTI: A research team member will deliver the BBTI intervention. BBTI consists of four main behavioural modifications: reduce time in bed, standardise sleep and wake times, go to bed only when sleepy and stay in bed only if asleep (i.e., stimulus control and sleep restriction) (Gunn et al. 2019). An overview of the four sessions is described in Appendix S5. BBTI was developed to address the shortcomings of CBT‐I whilst building on its success as a first line treatment for insomnia. Delivery of BBTI does not require specialised sleep medicine training. BBTI offers a simple, acceptable and effective treatment that can be implemented in a variety of medical settings. The efficacy of BBTI has been established in older adults and insomnia patients via a synthesis of RCTs (Chen et al. 2023). The BBTI will be delivered remotely or in person as determined through discussion with the participant and research team member.

Sleep hygiene education: Participants will be asked to adhere to 10 sleep hygiene principles that have been shown to improve sleep (e.g., reduce afternoon/evening caffeine intake; Appendix S6). Sleep hygiene consists of adjustments to sleep‐related behaviour and environment. Participants will be provided with a written document outlining each principle.

Behaviour change techniques: The PSP will use behaviour change techniques previously shown to be important for health behaviour change: (Rayward et al. 2020) goal‐setting, social support, self‐monitoring, feedback and graded tasks. The participant in collaboration with the researcher will set sleep‐related SMART (specific, measurable, attainable, realistic and time‐bound) goals. To mobilise the social environment, the participant will be asked to share their goal with one other person. The research team member will also use self‐monitoring, feedback and graded tasks (i.e., behaviour change techniques) to facilitate adherence to the BBTI and sleep hygiene components. For example, participants may start with a focus on five sleep hygiene principles before incorporating the rest. The wrist‐worn activity tracker will also be used for self‐monitoring, feedback and graded tasks. Each behaviour change component will seek to establish behavioural intentions and improve self‐efficacy, the participant's confidence in their ability to change behaviour. The techniques will also be used to minimise attrition.

